## Abstract

**Background:**

Transitions in care are vulnerable periods in health care that can expose patients to preventable errors due to incomplete or delayed communication between health care providers. Transitioning critically ill patients from intensive care units (ICUs) to other patient care units (PCUs) is particularly risky, due to the high acuity of the patients and the diversity of health care providers involved in their care. Instituting structured documentation to standardize written communication between health care providers during transitions has been identified as a promising means to reduce communication breakdowns. We developed an evidence-informed, computer-enabled, ICU-specific structured tool—an electronic transfer (e-transfer) tool—to facilitate and standardize the composition of written transfer summaries in the ICUs of one Canadian city. The tool consisted of 10 primary sections with a user interface combination of structured, automated, and free-text fields.

**Objective:**

Our overarching goal is to evaluate whether implementation of our e-transfer tool will improve the completeness and timeliness of transfer summaries and streamline communications between health care providers during high-risk transitions.

**Methods:**

This study is a cluster-specific pre-post trial, with randomized and staggered implementation of the e-transfer tool in four hospitals in Calgary, Alberta. Hospitals (ie, clusters) were allocated randomly to cross over every 2 months from control (ie, dictation only) to intervention (ie, e-transfer tool). Implementation at each site was facilitated with user education, point-of-care support, and audit and feedback. We will compare transfer summaries randomly sampled over 6 months postimplementation to summaries randomly sampled over 6 months preimplementation. The primary outcome will be a binary composite measure of the timeliness and completeness of transfer summaries. Secondary measures will include overall completeness, timeliness, and provider ratings of transfer summaries; hospital and ICU lengths of stay; and post-ICU patient outcomes, including ICU readmission, adverse events, cardiac arrest, rapid response team activation, and mortality. We will use descriptive statistics (ie, medians and means) to describe demographic characteristics. The primary outcome will be compared within each hospital pre- and postimplementation using separate logistic regression models for each hospital, with adjustment for patient characteristics.

**Results:**

Participating hospitals were cluster randomized to the intervention between July 2018 and January 2019. Preliminary extraction of ICU patient admission lists was completed in September 2019. We anticipate that evaluation data collection will be completed by early 2021, with first results ready for publication in spring or summer 2021.

**Conclusions:**

This study will report the impact of implementing an evidence-informed, computer-enabled, ICU-specific structured transfer tool on communication and preventable medical errors among patients transferred from the ICU to other hospital care units.

**Trial Registration:**

ClinicalTrials.gov NCT03590002; https://www.clinicaltrials.gov/ct2/show/NCT03590002

**International Registered Report Identifier (IRRID):**

DERR1-10.2196/18675

## Introduction

### Background

Complete and timely communication between health care providers is integral to seamless transitions in care [1-3]. The transfer of critically ill patients from the intensive care unit (ICU) to another patient care unit (PCU) is a particularly vulnerable period in patient care, due to the high acuity of patients [4-6] as well as the number of health care providers involved and their professional diversity [7-10]. The movement of patients between units requires a high degree of collaboration, with verbal and written communication between health care providers [1-3] as well as patients and families [1,11-13]. Suboptimal communication during transitions can have profound implications for patients, families, and the health care system [14-16], including increased risk of preventable medical errors, adverse events, redundant testing, readmissions, and dissatisfaction with the quality of care [17-24].

An ICU transfer summary is a clinical document that ICU physicians and nurse practitioners (NPs) often prepare to describe a patient’s stay in the ICU, including active and resolved health issues and the current care plan. The transfer summary is intended to support verbal communication between transferring and accepting medical teams and should provide sufficient detail to serve as a stand-alone communication [25]. Complete and timely exchanges of patient care information during transitions in care are critical, not only for immediate continuity of care but also for efficient coordination of future care [26,27]. As such, the transfer summary should be easily accessible to inpatient and outpatient health care providers as part of the patient’s permanent health care record.

Standardized transfer protocols that structure documentation are integral for preventing failures in patient care due to incomplete and delayed exchange of information [21,28-30]. However, their value can be limited by the very methods used to produce the document. While quick for the clinician to prepare, traditional methods like dictation or handwritten notes in the patient chart have been associated with inaccurate, incomplete, and lengthy delays in communication [17,20,31,32], particularly in comparison to transfer summaries prepared using electronic standardized tools [26,33-39]. The advancements of clinical information systems (CISs) and integrated electronic medical records (EMRs) provide a prime opportunity to optimize text-based communication. Structured templates can facilitate completeness of important patient information as well as substantiate and prompt verbal communication between health care providers at the point of care. They can also provide flexibility, permitting physicians to create a “living” document that can be edited over the course of stay and finalized at the point of patient transfer, effectively facilitating clinical workflow in complex settings. Despite the potential for optimizing efficient interprovider communication, the use of standardized tools to prepare ICU transfer summaries has not been widespread, with factors such as usability [39], cost, and workload [40] being barriers to adoption.

### Local Initiative to Standardize Transfer Summaries: The Electronic ICU Transfer Tool

In 2017, we began designing an evidence-informed, computer-enabled, ICU-specific communication tool in the primary, integrated patient care CIS—Sunrise Clinical Manager (Eclipsys Corporation)—used in four acute care hospitals in a single Canadian city. This work was initiated as a quality improvement project to improve upon the conventional system of dictation that physicians and NPs—herein called ICU clinicians—use to prepare medical transfer summaries for ICU patients [41]. To dictate a summary, ICU clinicians use eScription, 2010 release (Nuance Communications), a health information management dictation, speech recognition, and transcription (DST) platform. The clinician verbalizes relevant patient transfer information to create a voice file that is run through speech recognition software to create a text report. The report is then edited by a transcriptionist and sent to the designated ICU clinician for approval before being uploaded for electronic viewing in the CIS as well as to a provincial, web-based health data repository accessible by community-based physicians (Alberta Netcare).

The content and structure of the ICU electronic transfer (e-transfer) tool was based on a national survey of existing transfer summary tools [42], subsequent consensus-based recommendations of two independent multidisciplinary groups of health care providers [41,43], and a heuristic evaluation [41]. The e-transfer tool consists of 10 overarching document sections: visit data, goals of care, allergy and intolerances, diagnoses and visit issues, course in ICU, investigations, medications, discharge to home or community, send copies to, and completion. These sections are designed with a user interface combination of structured fields (eg, checkboxes); automated fields, which pull in relevant patient data from other CIS locations; and free-text fields (see Figure 1). The tool permits ICU clinicians to open an ICU summary as a clinical document directly in the patient’s EMR and edit the summary over the course of the patient’s ICU stay. As with the DST system, the designated ICU clinician must approve transfer summaries. The summaries remain in the CIS and are uploaded to the provincial repository.

**Figure 1 figure1:**
[figure not shown]
Electronic transfer tool sections and screenshots. ICU: intensive care unit.

In a small pilot test of the e-transfer tool in one ICU [42], electronic summaries had a significantly greater proportion of essential information fields completed overall (median 87.5%) than those prepared by dictation (median 62.5%) and were available to receiving teams closer to patient release (2.3 versus 45.0 hours). Primary users of the e-transfer tool also responded positively to its use, establishing favorable evidence to scale up implementation across additional municipal hospitals.

### Objective

In this study, we will evaluate the effectiveness of the ICU e-transfer tool for improved completeness and timeliness of transfer summaries and reduced adverse patient outcomes by comparing transfer summaries produced postimplementation to those produced preimplementation.

### Conceptual Framework

We will apply the Donabedian three-pronged model of health care quality (ie, structure, process, and outcome) [44] and the National Health Service Sustainability Model [45] to frame our evaluation of the e-transfer tool. The Donabedian model has been successfully used in multiple contexts to support quality improvement initiatives related to structures (ie, health care context), processes (ie, actions and events in health care), patient outcomes (ie, effects on health status, quality, knowledge, or behavior), and use of resources [46,47]. Similarly, the National Health Service Sustainability Model has been successfully used to predict the likelihood of sustainability for improvement initiatives [48]. In drawing from each of these models, we will ensure that we identify areas that need strengthening and that we are well positioned for sustainability and continual improvement.

## Methods

### Setting

This evaluation study takes place in four acute care hospitals servicing a single city, Calgary, Alberta, Canada, which has a referral population of approximately 1.7 million. Three of the four hospitals are academic hospitals operating a combined 56 adult medical-surgical ICU beds; the fourth is a nonacademic, community-based hospital operating 10 ICU beds. The annual ICU admission rate across the city approximates 3000 patients. In addition to the CIS hosting the e-transfer tool (ie, Sunrise Clinical Manager), all ICUs also use a dedicated provincial critical care CIS (ie, eCritical MetaVision) and clinical analytics system (ie, eCritical TRACER) that capture key demographic, clinical, health care service, and outcome data for all ICU patients [49]. ICUs are staffed by multidisciplinary teams; those in academic-based hospitals operate with a clinical fellow and 4 to 10 residents working under the supervision of an attending physician. One ICU has an NP. Critical care resident rotation blocks are 4 weeks in duration. The community-based ICU functions with an attending physician and 4 NPs.

### Study Design

This study uses a cluster-specific pre-post trial design with randomized and staggered implementation of the e-transfer tool across four hospitals.

### E-Transfer Tool Implementation

The e-transfer tool has been sequentially implemented into the four study hospitals at a new site every 2 months. This occurred between July 2018 and January 2019. The study biostatistician (AS), who was not involved with clinical practice in the ICUs, randomized the order of hospitals for implementation. Dictation remained available after implementation, but the ICU e-transfer tool was endorsed as the primary method to prepare ICU transfer summaries; as well, use of the tool was supported with strategies that have been successfully used in previous local initiatives, including in-person and web-based education, point-of-care support, and electronic audit and feedback [50].

### Participants

ICU patients from the four participating hospitals were eligible for inclusion in the study if the patient (1) was admitted to the ICU during the defined pre-post periods; (2) was 18 years of age or older; (3) had an ICU stay equal to, or longer than, 24 hours; and (4) was transferred from the ICU to an in-hospital PCU. Patient admission lists were extracted retrospectively by a data analyst with the critical care CIS repository (ie, eCritical TRACER). As the primary creators of most ICU transfer summaries [42], NPs and residents were invited to participate in a brief survey soliciting their experience creating transfer summaries.

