### Data Collection

#### Overview

We set pre- and postimplementation data collection periods to extend for 6 months each, based on the staggered dates when the ICU e-transfer tool was implemented at each hospital. Patients transferred from the ICU prior to the intervention implementation date of their hospital are considered in the preimplementation period, while patients transferred from the ICU on or after the intervention implementation date of their hospital are considered in the postimplementation period.

Data collection involves (1) electronic extraction from provincial system repositories and a local critical care database, (2) manual abstraction from the patient’s electronic and paper medical record by trained researchers, and (3) manual rating of sampled transfer summaries by clinicians. Survey data of ICU clinician perspectives was collected pre- and postimplementation of the e-transfer tool. The flow of data collection is shown in Figure 2. Where feasible, we are deidentifying hospital name, dates, and clinician and patient identifiers from clinical documents (eg, transfer summaries and clinician progress notes) secured for manual data abstraction. All data will be encrypted and retained in a secured office.

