#### Sample Size Calculations

Sample size calculations were based on the cluster-specific pre-post study design. Based on our pilot [41,42], we calculated a required sample size of 144 pre- and 144 postimplementation ICU transfer summaries from each hospital to assess our primary outcome. This will be sufficient to detect an absolute difference in our primary outcome of 15% for each hospital with 82% power and an α value of 5% based on a baseline proportion of 20%; we observed a change in our pilot from 23% to 83%. A random sample of 24 ICU patients per hospital per month, over 6 months pre- and 6 months postimplementation, will facilitate secondary analyses, which accommodate the possibility of secular trends. The study biostatistician (AS) determined the random sample by assigning computer-generated random numbers to the complete list of patients transferred from each ICU within the study period, which was extracted by a data analyst with the critical care analytics system (see Figure 2). The study biostatistician was blinded to the method used to create the summary at the time of randomization.

To collect clinician ratings of the transfer summary quality, we calculated requiring 64 summaries preimplementation (ie, 16 per hospital × 4 hospitals = 64) and 64 summaries postimplementation (ie, 16 per hospital × 4 hospitals = 64), which will be sampled from aforementioned summaries, to detect an absolute difference in means as small as 0.5, assuming an SD of 1, with 80% power and an α value of 5%. The same patient cases will be used to assess for suspected post-ICU adverse events.

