## Results

Based on our study design, in fall 2019, the eCritical data analyst completed preliminary extraction of the list of patients transferred from the ICU within the 18-month range: February 12, 2018, to June 30, 2019. We have randomly sampled eligible patients from each ICU, restricting sampling to 6 months before and 6 months after the date the e-transfer tool was implemented in the hospital. Abstraction of primary and secondary outcomes is underway. We anticipate all data to be collected by early 2021, with data cleaning and analyses conducted and first results ready for publication in spring or summer 2021.

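### Eligibility is set by ICU admission date, but period, sampling frame and extraction by transfer date; applied as written, this loses long stays from the start of the pre window only (minor)

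*Protocol article*

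**What the plan says.** Four places in the protocol article bear on who enters the sample.

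- **Methods, Participants, criterion 1.** The patient "was admitted to the ICU during the defined pre-post periods". The anchor is ICU admission.
- **Methods, Data Collection, Overview.** "We set pre- and postimplementation data collection periods to extend for 6 months each", set separately for each hospital. The pre rule reads: "Patients transferred from the ICU prior to the intervention implementation date of their hospital are considered in the preimplementation period". The post rule mirrors it with the same anchor and takes in the implementation date itself: "patients transferred from the ICU on or after the intervention implementation date of their hospital are considered in the postimplementation period". The anchor is transfer, and the two windows meet at the implementation date with no gap.
- **Methods, Sample Size Calculations.** Random numbers were assigned to "the complete list of patients transferred from each ICU within the study period". The design is "A random sample of 24 ICU patients per hospital per month, over 6 months pre- and 6 months postimplementation". The anchor is transfer.
- **Results.** The article reports "extraction of the list of patients transferred from the ICU within the 18-month range: February 12, 2018, to June 30, 2019", and then "We have randomly sampled eligible patients from each ICU, restricting sampling to 6 months before and 6 months after the date" of implementation. The list is anchored on transfer, but the draw is described as being from eligible patients, which brings criterion 1 back in.

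Methods, Data Analysis compares ICU and hospital length of stay by Wilcoxon rank-sum test. The primary-outcome models adjust for ICU length of stay, APACHE II, SOFA, GCS, the Charlson index and ICU therapies, among other covariates.

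**The concern.** Admission and transfer dates differ by the length of the ICU stay, so a rule that mixes them selects on length of stay. Take the rules together, as written:

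- A patient admitted before the pre window opens and transferred inside it is on the transfer list but fails criterion 1.
- A patient admitted in the pre window and transferred after implementation meets criterion 1 and counts as post.

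Long stays are therefore removed at the opening of the pre window. At the opening of the post window they are kept. Because 24 patients are drawn per month whatever the size of the list, the lost places are filled by other patients, who tend to have shorter stays. The outcomes directly exposed are ICU stay and hospital stay, which contains it, since both are compared without adjustment. An eligibility sentence could then make stays look longer after the tool when nothing has changed.

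**Working it through.** **Plan figures.** 24 per month × 6 months = 144 per period per hospital, as stated. The stated 82% power for 20% versus 35% with 144 per period reproduces at 81.7% (two-sided 5%). Neither figure depends on this point. The article gives no ICU stay distribution, so the sizes below are assumption-based.

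**Formula.** Let L be the ICU stay and t the transfer time in days after the pre window opens. With a steady flow, t is uniform. A transfer is excluded when L > t, so the share lost among the first T days of transfers is E[min(L, T)] / T. For six months (T = 365.25/2 = 182.6 days) almost all stays are shorter than T, and the share is close to mean stay / 182.6:

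- mean 4.45 days: 4.45/182.6 = 2.4%
- mean 6.34 days: 6.34/182.6 = 3.5%
- mean 8.66 days: 8.66/182.6 = 4.7%

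A post transfer is lost only if the stay exceeds the time since the pre window opened, which is at least 182.6 days. That is essentially never.

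**Simulation.** Lognormal stays restricted to one day or more (the 24-hour criterion), uniform transfer dates over 12 months, and criterion 1 applied literally. Each month has equal weight, as in the sampling design.

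| Assumed median (days) | Mean (days) | Lost, pre month 1 | Lost, whole pre | Lost, post | Mean stay, month 1 as sampled | Mean stay, pre as sampled | Mean stay, post |
|---|---|---|---|---|---|---|---|
| 3.3 | 4.45 | 14.6% | 2.4% | 0.0% | 3.89 | 4.35 | 4.45 |
| 4.3 | 6.34 | 20.3% | 3.5% | 0.0% | 4.87 | 6.04 | 6.34 |
| 5.3 | 8.66 | 26.2% | 4.7% | 0.0% | 5.60 | 7.88 | 8.66 |

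- *Mean stay.* The pre mean falls by 0.10, 0.30 and 0.78 days. Other runs with similar medians put the fall between 0.07 and 1.0.
- *Month 1 places.* 24 × 0.146 = 3.5, 24 × 0.203 = 4.9 and 24 × 0.262 = 6.3 of the 24 places per hospital go to other patients.
- *Stays of 14 days or more.* 63-73% of those transferred in pre month 1 are lost, and 11-15% over the whole pre period.

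**Effect on the Wilcoxon test of ICU stay.** With no true effect and assumed medians of 3.0 to 5.5 days, rejection at nominal 5% is about 4-9% within a hospital (144 v 144; values below 5% are simulation noise). With all four hospitals pooled (4 × 144 = 576 v 576) it is about 6-20%. The excess runs almost entirely toward longer stays post. The pre median falls by about 0.03-0.3 days. Hospital stay was not simulated. It should move in the same direction because it includes the ICU stay.

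**Effect on the primary outcome.** Suppose patients staying 14 days or more have a primary-outcome rate 5 to 20 points below the 20% baseline (an assumption). In the three scenarios the pre proportion shifts by 0.01 to 0.4 points before any adjustment, against a design difference of 15 points.

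**Heavier stays.** With assumed medians of 7.2 and 7.6 days (means 11.8 and 15.2), the whole-pre loss rises to 6.4% and 8.1% and the month 1 loss to 33% and 37%. The pre mean falls by 11.82 − 10.33 = 1.5 and 15.18 − 11.65 = 3.5 days. The primary shift is still at most about 1 point.

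**The case against.** **The loss may never have happened.** A reader might infer that long-stay patients have been removed. The article does not say that an admission-date filter was run, and every operational statement uses transfer. The wording is also loose: Participants speaks of admission lists where Results speaks of a list of transferred patients. Criterion 1 may simply mean ICU patients in the study periods, in which case nobody is lost and one sentence is wrong. This stands, and the bias must be stated as conditional. It does not remove the point, because Results says eligible patients were sampled, so literal use cannot be ruled out.

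**Another reading would be symmetric.** If criterion 1 meant admission and transfer in the same period, both openings would be truncated about equally (for example 3.5% and 3.5% in the middle scenario). The text does not say this.

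**The consequences are limited.** This also stands. A reader might infer harm to the primary result, but the primary models adjust for ICU stay and severity, and even the unadjusted shift is small. A reader might also infer a distorted secular trend or a lighter pre case mix. The pooled model with the time term carries the same covariates, no effect on any modelled outcome has been shown, and the article gives no link between stay and severity. Within a hospital the Wilcoxon test is barely disturbed. The article does not say outright that the Wilcoxon test will be pooled, although it plans within-hospital and pooled analyses of secondary outcomes.

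**Conclusion.** The contradiction is in the text: one eligibility criterion uses admission date, and the period rule, frame and extraction use transfer date. Applied as written, the rules drop long stays from the start of the pre period and essentially nowhere else. For assumed lognormal stays with medians of about 3 to 5.4 days, the loss is about 2-5% of pre transfers, concentrated in month 1 (14-26%), and the pre mean stay is about 0.1-1 day too short. The result is a modest bias in secondary, unadjusted length-of-stay comparisons, toward longer stays after the tool. It is material mainly in a pooled test with the longer assumed stays.

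These sizes rest on the assumed distribution, a steady flow of transfers, and literal use of criterion 1. The documents do not support saying that the bias has occurred or that the primary outcome is threatened. Severity: minor.

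**What to change.** Reword criterion 1 as transfer from the ICU within the hospital's 6-month pre or 6-month post window, whatever the admission date. Participants, Data Collection, Sample Size Calculations and Results then agree, and exclusion by this route is zero in every month. The sample stays at 144 + 144 per hospital and power at about 82%. The cost is one sentence.

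Then check with the data analyst and the biostatistician whether an admission-date filter was used when the sample was drawn. If it was not, nothing more is needed. If it was, either redraw the affected pre month 1 patients (on the assumptions above, about 3.5 to 6.3 of 24 per hospital) or report a length-of-stay sensitivity analysis without that month. Results says abstraction is still under way, so a small redraw is feasible.
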